## 2. Materials and methods

### 2.1. Aim of the study, design and setting

The overall aim of the VOICE-DEP study is to develop and formalize a standardized, reproducible and clinically grounded protocol for the multimodal analysis of voice and speech during medical interviews as a tool to support the diagnosis and longitudinal monitoring of depressive disorder.

The working hypothesis is that major depressive disorder and its clinical evolution are associated with changes in acoustic, paralinguistic and linguistic characteristics of voice and speech, and that these changes can be analyzed in a standardized and reproducible manner in a routine clinical setting.

**Primary objective.** The primary objective is to establish a reproducible clinical framework for extracting and analyzing acoustic, paralinguistic and linguistic features from semi-structured medical interviews, allowing discrimination between patients with a medical diagnosis of depressive disorder and healthy controls using voice-based models anchored to validated clinician-rated clinical reference standards.

**Secondary objectives.** The secondary objectives are: i) To construct a longitudinal Spanish-language clinical speech corpus including repeated voice recordings from patients with depressive disorder and single-session recordings from healthy controls; ii) To characterize the association between speech-derived digital biomarkers and clinician-rated measures of depressive severity, including their evolution over time; iii) To evaluate the added value of multimodal models combining acoustic, paralinguistic and linguistic features compared with unimodal models; iv) To assess intra-individual vocal changes across repeated assessments and their association with changes in clinical severity; v) To provide a transparent methodological framework that may facilitate replication, cross-study comparison and future external validation in other clinical presentations, diagnoses, languages and sociocultural settings; vi) To explore whether specific treatment modalities are associated with greater changes in voice and speech in parallel with clinical evolution.

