### 2.2. Study population and participant characteristics

The study will include two groups: (1) patients with a medical diagnosis of moderate or severe unipolar depression and (2) healthy control participants without a personal history of depression or any other psychiatric disorder.

Inclusion criteria for patients are: Age 18 years or older; Native Spanish speakers or individuals with sufficient fluency in Spanish to maintain a clinical interview; Capacity to understand study procedures and provide written informed consent, according to the investigator’s judgement; Medical diagnosis of moderate or severe unipolar depression, with or without psychotic symptoms, according to ICD-10 categories: moderate depressive episode (F32.1), severe depressive episode without psychotic symptoms (F32.2), severe depressive episode with psychotic symptoms (F32.3), recurrent depressive disorder, current episode moderate (F33.1), recurrent depressive disorder, current episode severe without psychotic symptoms (F33.2), or recurrent depressive disorder, current episode severe with psychotic symptoms (F33.3), regardless of whether the patient receives psychotherapeutic, pharmacological or neurostimulation treatment, or chooses not to receive active treatment while remaining under clinical follow-up.

Exclusion criteria for patients are: Severe neurological disorders affecting speech production or cognitive function, such as severe dementia; Severe voice or speech disorders unrelated to depression that prevent completion of the clinical interview through verbal language; State of intoxication due to substance use at the time of assessment; Other severe medical conditions interfering with study participation or speech production.

Inclusion criteria for healthy controls are: Age 18 years or older. Exclusion criteria for healthy controls are: Personal history of depression or any other psychiatric disorder; Severe neurological disorders affecting speech production or cognitive function, such as severe dementia; Severe voice or speech disorders unrelated to depression that prevent completion of the clinical interview through verbal language; State of intoxication due to substance use at the time of assessment; Other severe medical conditions interfering with study participation or speech production.

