**Table 2 pone.0353827.t002:** Study variables recorded in the VOICE-DEP case report form and assessment schedule.

Domain	Description	Assessment visits
Participant identification	Participant category (patient or control), study code, and visit date	V0–V4 in patients; V0 in controls
Sociodemographic and anthropometric baseline variables	Sex, age, marital status, place of residence, birth order in the sibship, height, weight, body mass index, body surface area, educational level, childcare responsibilities, caregiving responsibilities for dependent relatives, religious belief, community religious practice, and social relationships	V0 only
Lifestyle, family history and contextual baseline variables	First-degree family psychiatric history, toxic habits, tobacco, alcohol, cannabis, cocaine, amphetamine and other substance use, physical activity, diet pattern, complementary or alternative treatments and specific prescribed diets, pharmacogenetic or pharmacodynamic isoform information when available, employment status, night work, acute and chronic stressful life events, and current and lifetime traumatic events	V0 only
Clinical baseline variables	Principal diagnosis according to ICD-10 depressive categories, psychiatric comorbidities, medical comorbidities, previous suicidal ideation, previous suicidal behavior, previous self-harm, duration of the current episode, time since initial diagnosis, and number of previous depressive episodes	V0 only
Recording and audio traceability variables	Whether the voice recording was obtained, pseudonymized audio file identifier, presence of recording incidents, and type of incident (patient need, clinical need, technical problem, others)	V0–V4 in patients; V0 in controls
Clinician-rated and self-reported symptom variables	Depressive symptom severity assessed with MADRS, global clinical impression assessed with CGI, and self-reported depressive symptom burden assessed with PHQ-9	V0–V4 in patients; V0 in controls
Pharmacological treatment variables	Pharmacological treatment received, including total daily dose in mg/24h, dosing interval, administration time, and duration of treatment at the recorded dose	V0–V4 in patients
Non-pharmacological treatment and psy-chotherapy variables	Sleep hygiene measures, diet pattern, regular physical activity, discontinuation of toxic habits, psychotherapy attendance, psychotherapy type, and psychotherapy frequency	V0–V4 in patients

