Psychotic status will be considered as a potential confounder and included as a binary covariate when the sample permits stable estimation. Sensitivity analyses excluding patients with psychotic depression will be performed, while subgroup comparisons will be considered exploratory.

Regularized logistic regression will be the primary classification model, with a linear support vector machine and random forest models used for comparison. Missing data, including their frequency, pattern, and documented reasons, will be reported by variable and visit. Mixed-effects models will include a participant-specific random intercept, time as a fixed effect, and selected time-varying covariates; a random slope for time will be considered if supported by the data. The Benjamini–Hochberg procedure will control the false discovery rate within each feature family, and feature selection and hyperparameter tuning will be performed within each training partition.

Because repeated recordings from the same patient are not independent, all longitudinal analyses, predictive modeling and validation procedures will use participant-level data splitting and account for within subject correlation, in order to preserve the independence of training and test data. Specifically, all recordings from the same participant will be assigned exclusively to either the training or the test partition, in order to reduce optimistic bias due to repeated observations from the same individual and avoid information leakage. In this context, Leave-One-Group-Out cross-validation will be used as an appropriate validation framework for grouped repeated-measures data.

To improve clinical interpretability, feature attribution analyses will be performed using Shapley-based methods, including SHAP values where applicable. These analyses will help identify which acoustic, paralinguistic, and linguistic signals contribute most strongly to model predictions and will support the interpretation of the relative importance of different multimodal domains. No imputation for missing data will be applied. To maximize the data collection, quality control reviews will be conducted after every visit. A flexible time-window for visits and periodic reminder phone calls will be planned to reduce the risk of follow-up losses.

All analyses will be performed using Python v3.x or equivalent validated statistical software. Statistical significance will be considered at a two-sided threshold of p < 0.05.

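### Controls are screened for any psychiatric history and patients are not, so the patient-control AUC reflects depression together with its comorbidity and cannot by itself be credited to depressive disorder

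*Protocol article*

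**What the plan says.** **Eligibility (Section 2.2).** Patients need a "Medical diagnosis of moderate or severe unipolar depression, with or without psychotic symptoms, according to ICD-10 categories". Their exclusions cover severe neurological disease, severe voice or speech disorders, intoxication at assessment and other severe medical conditions; none concerns a second psychiatric diagnosis. The same four apply to controls, with one more: "Exclusion criteria for healthy controls are: Personal history of depression or any other psychiatric disorder".

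**What is to be shown (Sections 2.1 and 2.6).** The primary objective is a framework "allowing discrimination between patients with a medical diagnosis of depressive disorder and healthy controls using voice-based models". The overall aim is a tool that helps to diagnose and monitor depressive disorder. The working hypothesis ties speech changes to major depressive disorder, and the exposure variable is the diagnosis of unipolar depressive disorder.

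**What is collected (Table 2).** The baseline clinical variables include "Principal diagnosis according to ICD-10 depressive categories, psychiatric comorbidities, medical comorbidities", so the protocol expects some patients to have a further psychiatric diagnosis.

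**What is done with it (Sections 2.4 and 2.7).** Matching is on age and sex. The named between-group covariates are age, sex, education and socioeconomic variables. Every case report form variable will be described, which includes comorbidity. The one psychiatric confounder named is psychotic status, with a covariate where feasible and a restriction: "Sensitivity analyses excluding patients with psychotic depression will be performed, while subgroup comparisons will be considered exploratory". The limitations in Section 3.1 do not mention other psychiatric comorbidity.

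**The concern.** The entry rules make the groups differ in two respects: depression, and every other psychiatric disorder past or present. A comorbid disorder that alters speech moves the patient distribution and is counted in the group difference and in the AUC. A feature could separate the groups wholly or partly because of an accompanying condition and still be carried forward as a candidate marker of depression.

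Covariate adjustment across the groups cannot repair this. Every control has comorbidity equal to zero by rule, so the controls hold no information about its effect. Only restriction or stratification among the patients can address it. The plan uses that approach for psychotic depression but states nothing similar for other comorbidity, although the variable is already in the case report form.

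**Working it through.** **1. The plan's own figure.** Section 2.4 gives a detectable d of about 0.70 for 25 patients and 50 controls, two-sided 0.05, 80% power. A two-sample t-test gives 0.695, and power of 80.5% at d = 0.70. The figure reproduces. It serves here only as a yardstick.

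**2. Inputs that the documents do not give.** Neither the share p of comorbid patients nor the shift d_c (in SD) that comorbidity adds to a feature is stated. The ranges below are assumptions: p = 30–60%, d_c = 0.3–0.8. The model takes the shift as additive to the depression effect, with equal variances and, unless stated otherwise, in the same direction.

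**3. Shift in the group difference.** Shift = p × d_c.
- Low end: 0.30 × 0.3 = 0.09 SD, or 13% of 0.70.
- Middle: 0.50 × 0.5 = 0.25 SD, or 36% of 0.70.
- High end: 0.60 × 0.8 = 0.48 SD, or 69% of 0.70.

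**4. A feature unrelated to depression.** The chance that a single unadjusted t-test (df 73) finds a patient-control difference uses noncentrality = shift × √(25 × 50 / 75) = shift × 4.08.
- 0.09 SD: 6.5%.
- 0.25 SD: 17.2%.
- 0.48 SD: 49%.

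The reference value is 5%. These are not false positives for the contrast patients versus healthy controls, where the group difference is real. They are misattributions only if the finding is read as an effect of depression.

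**5. AUC of one feature with a depression effect of 0.70.** Without comorbidity, AUC = Φ(0.70/√2) = 0.690. With it, AUC = (1 − p) Φ(0.70/√2) + p Φ((0.70 + d_c)/√2).
- p = 0.3, d_c = 0.3: 0.7 × 0.690 + 0.3 × 0.760 = 0.711.
- p = 0.5, d_c = 0.5: 0.5 × 0.690 + 0.5 × 0.802 = 0.746.
- p = 0.5, d_c = −0.5 (opposite direction): 0.5 × 0.690 + 0.5 × 0.556 = 0.623.

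The sign matters: comorbidity can raise or lower the AUC of a feature.

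**6. What a restricted analysis could show.** With 30–60% of 25 patients removed, 25 × 0.70 = 17.5 to 25 × 0.40 = 10 remain, so about 10 to 17. Against 50 controls (t-test, 80% power; Hanley–McNeil standard error at AUC 0.69):

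| Patients left | Detectable d | SE of AUC | 95% half-width |
|---|---|---|---|
| 17 | 0.80 | 0.079 | 0.155 |
| 10 | 0.99 | 0.099 | 0.195 |

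The same formula gives a half-width of 0.13 for all 25 patients. The same-direction shifts worked in step 5 are 2 to 6 AUC points, well inside these intervals.

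**The case against.** The strongest reply is that the design delivers what the primary objective asks for: patients with diagnosed depression against healthy controls, with healthy defined in Section 2.2. This stands. A reader might infer that the AUC contradicts the primary objective; the documents do not support that. The gap lies between the contrast and the attribution made in the aim, the hypothesis and the exposure definition.

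A reader might also infer that the comorbidity variable is never used. That goes too far as well: Section 2.7 describes all case report form variables, so the comorbid share should be reported. What is absent is any stated between-group analysis that uses it.

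The protocol is modest in its claims. Classifier results are called exploratory, Section 3.1 treats speech measures as complements to clinical assessment, and the secondary objectives look to later validation in other diagnoses. This limits the harm. But the stated grounds for caution are pilot status and sample size, which concern precision. A larger study under the same entry rules would have the same composition problem with a narrower interval.

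A journal article need not list every sensitivity analysis, and unrestricted patients against screened controls is an ordinary first-stage design. The case for raising the point is that the article does choose which psychiatric confounder to handle and names psychosis alone.

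Finally, the magnitude is all assumption, and the percentages in step 4 ignore the planned Benjamini–Hochberg control. Both remarks are right. The figures show scale under stated inputs and are not evidence of bias in this study.

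**Conclusion.** The point holds in a limited form. The baseline contrast and AUC reflect depression together with its psychiatric comorbidity against people with no psychiatric history. That satisfies the primary objective as written but does not by itself support attributing the difference to depressive disorder.

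The size of any bias is unknown, and its direction may differ between features. Under the assumed same-direction ranges the group difference moves by 0.09 to 0.48 SD; at the low and middle settings an AUC of 0.69 becomes 0.71 or 0.75. An opposite shift lowers it.

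The scope is confined to the patient-control analyses. Severity associations and trajectories studied within patients do not rest on this contrast. Psychotic depression already has its own restriction, and intoxication at assessment is excluded. This is a worthwhile, cheap improvement, not a flaw that undermines the study.

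**What to change.** **Section 2.7, beside the analysis that excludes psychotic depression.** Add that the baseline patient-control comparison and the primary classifier (regularized logistic regression) will be repeated without patients who have a recorded psychiatric comorbidity. Report the result with its confidence interval and the number of patients left, labelled as a consistency check only.

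**Sections 2.7 (discrimination analysis) and 3.1.** State that the AUC describes discrimination between patients with depression, with or without psychiatric comorbidity, and people with no psychiatric history, and that it is not evidence of specificity to depression.

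**Cost.** One further analysis on data already collected, and a sentence or two of text. Eligibility, visits and sample size stay as they are, and the change can be written down before the analysis planned for February 2028. The drawback is precision: on the assumed 30–60% comorbid share, the restricted analysis can neither confirm nor rule out a shift of a few AUC points. The wording change therefore carries most of the benefit.

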### 2.3. Study procedures and visit schedule

Participants will be recruited consecutively according to eligibility criteria. Patients will be invited by physicians from the research team during routine clinical practice. Healthy controls will be invited by members of the research team and, if they agree to participate, will be referred to a physician from the research team for baseline assessment. As this is an observational study, no randomization or blinding procedures will be applied.

At the baseline visit (V0), all participants will receive verbal and written information about the study objectives, methodology, non-invasive nature of the procedures, confidentiality safeguards, and exclusive research use of the collected data. Written informed consent will be obtained before any study-related procedure. A clinical interview will then be conducted to collect baseline sociodemographic and clinical information, followed by psychometric assessment using the clinical instruments specified in the protocol. During the same session, voice recordings will be obtained under standardized conditions.

Only patients with depressive disorder will undergo longitudinal follow-up. Patients will attend four additional visits coinciding, whenever possible, with routine psychiatric follow-up visits: V1 at 30 days, V2 at 60 days, V3 at 90 days and V4 at 120 days, each with an allowed window of ±7 days. At each follow-up visit, the same recording and clinical assessment procedures applied at baseline will be repeated. Clinician-rated and self-reported measures of depressive severity will be updated, and relevant clinical changes, including treatment adjustments or adverse events, will be documented. Healthy controls will complete only the baseline visit under the same recording conditions.

In all participants, data collection will be integrated into the clinical interview. Only the part of the medical interview corresponding to the MADRS assessment will be audio recorded. In order to combine open ended questions by clinicians that allow patients to describe their experiences in their own words, allowing spontaneous and elaborated responses, while adopting a reliable method of exploration, the instructions of Montgomery and Asberg for the MADRS will be adopted, moving from broadly phrased questions about each symptom to more detailed ones which allow a precise rating of severity [27]. The recorded material will comprise the complete MADRS-related clinical interaction, including an initial free-speech segment immediately followed by the semi-structured questions used to complete the scale. The free-speech segment will be an introductory part of the recorded MADRS assessment (namely, patients will be asked to describe, in their own words, how they have been feeling in the past week). This recorded segment is expected to last approximately 10–30 minutes including the initial free-speech segment, allowing voice and speech to be collected within a clinically meaningful interaction while maintaining a standardized procedure.

Voice recordings will be assigned a pseudonymized audio identifier linked to participant type, participant code and visit number. Any relevant recording incident, including interruption due to patient need, clinical need or technical problems, will be documented in the case report form and considered in data quality assessment.

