### 2.5. Voice recording protocol

Voice recordings will be obtained using a Jabra Speak 510 USB omnidirectional microphone, positioned frontally at a distance of no more than 20 cm from the participant’s mouth. Recordings will be conducted in a quiet hospital room, with minimized background noise, closed doors and windows whenever feasible, silenced electronic devices, and no overlapping speech or external interruptions whenever possible.

The Jabra Speak 510 microphone was selected for pragmatic and translational reasons: it is affordable, widely available, easy to deploy and compatible with routine hospital use. This choice prioritizes ecological validity over laboratory-grade audio fidelity, which may reduce the precision of signal-sensitive measures such as jitter, shimmer, HNR, and intensity. This potential variability will be reduced by maintaining the same microphone, configuration, placement, and recording conditions throughout the study. This approach is consistent with previous studies that have used non-specialized recording devices, including tablet microphones, smartphone microphones and mobile phones, to extract clinically relevant speech and voice features [19,24,25,30].

Repeated assessments will be scheduled within a similar time-of-day window for each participant whenever feasible. Because recordings are integrated into routine clinical visits, exact consistency cannot be guaranteed; recording time will therefore be documented and considered in sensitivity analyses. Audio recordings will be stored in uncompressed WAV format to preserve signal integrity during feature extraction. All files will be labeled using pseudonymized alphanumeric identifiers. Speaker diarization will identify participant and interviewer segments, followed by manual review. Overlapping or uncertain segments will be excluded, and the original recording will be preserved unchanged. For acoustic and paralinguistic analyses, only participant speech will be retained. The complete interaction will be automatically transcribed and manually reviewed to correct transcription and speaker-attribution errors. Linguistic variables and contextual text embeddings will be extracted from the reviewed participant transcripts, while interviewer turns will be retained as conversational context.

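### The blanket no-blinding rule also leaves the manual reviewers of audio segments and transcripts unmasked, although an observational design does not require this

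*Protocol article*

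**What the plan says.** Section 2.3 sets the rule for the whole study: "As this is an observational study, no randomization or blinding procedures will be applied". It makes no exception for any role. The same section gives each recording a "pseudonymized audio identifier linked to participant type, participant code and visit number". Section 2.5 adds: "All files will be labeled using pseudonymized alphanumeric identifiers".

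Section 2.5 then describes two manual steps that follow automatic processing:

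- On the audio: "Speaker diarization will identify participant and interviewer segments, followed by manual review". The next sentence reads: "Overlapping or uncertain segments will be excluded, and the original recording will be preserved unchanged". Only participant speech is kept for the acoustic and paralinguistic variables.
- On the text: "The complete interaction will be automatically transcribed and manually reviewed to correct transcription and speaker-attribution errors". The linguistic variables and text embeddings are taken from the reviewed participant transcripts.

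Section 2.6 names the recording and the variables extracted from it as the primary outcome variables. Section 2.5 also requires two minutes of valid participant speech for the primary multimodal analysis.

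**The concern.** The primary outcomes are not purely machine-generated. A person settles which segments remain, who is speaking and which words stand. If that person knows whether the file comes from a patient or a control, whether it is V0 or V4, or what the MADRS score was, the editing may differ by group or visit without anyone intending it. Features such as pause ratio, speech rate, word count, voice quality and lexical measures could then carry a difference that comes from the editing.

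Two sets of results are exposed: the patient-control discrimination in the primary objective, and the association of within-patient speech change with clinical change in secondary objectives ii and iv (section 2.1). The pilot label does not remove the issue, because section 2.4 says the study is meant to evaluate standardization, reproducibility and analytical validity. The processing pipeline is therefore part of what is being tested.

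**Working it through.** **1. Does manual review precede the primary outcomes?** Yes. Acoustic and paralinguistic variables use the speech retained after diarization review, and linguistic variables use the reviewed transcript (section 2.5). Both are primary outcome variables (section 2.6). The step applies to 25 × 5 + 50 = 175 planned recordings. Automatic diarization and transcription come first, so reviewers finalize the content; they do not create it.

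**2. Does the stated reason cover this step?** No. An observational design excludes random allocation. Masking the people who process outcome data needs no allocation by the study.

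**3. Is there protection elsewhere?** None is stated. Pseudonymized labels (section 2.5) protect identity and are not said to conceal group or visit. The article gives no masked review, written criterion for an uncertain segment, second review or agreement check, and section 3.1 does not list reviewer knowledge among the limitations.

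**4. Would the validation scheme detect it?** No. Participant-level splitting and Leave-One-Group-Out validation (section 2.7) prevent leakage between recordings of one person. A group-related editing difference would already be in the features of both training and test participants, so held-out performance would reflect it too.

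**5. How large could it be?** The documents give no figure. The following is illustration only. First, the plan's own sizing figure (section 2.4: 25 versus 50, two-sided 0.05, 80% power, d about 0.70) reproduces:

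- SE = √(1/25 + 1/50) = √0.06 = 0.245
- Normal approximation: (1.960 + 0.842) × 0.245 = 0.686; two-sample t test: 0.695

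Now assume that editing shifts one feature by b SD between groups with no true difference. Rejection rate = Φ(b/SE − 1.96) + Φ(−b/SE − 1.96), and single-feature AUC = Φ(b/√2):

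| Assumed b | Rejection rate | AUC |
|---|---|---|
| 0 | 5.0% | 0.50 |
| 0.1 | 6.9% | 0.53 |
| 0.2 | 12.9% | 0.56 |
| 0.3 | 23.2% | 0.58 |
| 0.5 | 53.2% | 0.64 |

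The opposite sign can do harm as well. If the true difference is 0.70 and editing removes 0.20, 0.50 remains. By the same formula power is then 53.2%, against 81.5% at 0.70.

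**6. Does the two-minute threshold matter?** Only at the margin. If 5–15% of speech were discretionary (an assumption), dropping 15% takes a recording below 120 s only if it held less than 120/0.85 = 141 s (2:21). A recording with 300 s of participant speech would keep 300 × 0.85 = 255 s.

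**The case against.** The strongest case against has five parts.

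- **A link is not a label.** A reader might infer that group and visit can be read from the file name. The protocol does not say so: a link may be a separate key. This stands. What can be said is that nothing prevents reviewers from knowing.
- **The review is narrow.** The exclusion sentence directly follows the one on separating participant from interviewer, so an uncertain segment most naturally means one whose speaker is unclear. Transcript review is confined to correcting errors. A reader might picture reviewers judging mumbled or quiet speech as depressed or as noise, but no such criterion appears. This stands and limits the scope for judgement, although deciding who spoke, and what was said, still involves some.
- **The direction is unknown.** A reader might infer that the bias favours the hypothesis. The documents support no sign: dropping more unclear speech from patients could equally shrink a difference. This stands.
- **Group masking will often fail.** Every recording is a MADRS interview opening with an account of the past week, so content will often show who is a patient. This stands for the primary comparison. It applies less to visit number and not to access to scores.
- **This is operational detail in an exploratory pilot.** Who reviews, and in what order, is commonly left to a fuller document, and the preserved originals allow a later masked re-review. Both are true. However, the article does not merely omit masking: it rules it out in general terms, and a fuller document that masked reviewers would contradict that sentence.

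**Conclusion.** The concern holds in a limited form. The reason given for having no blinding does not extend to segment and transcript review, and that review settles the final content of the primary outcome variables. Nothing in the protocol keeps reviewers from knowing group, visit or scores. Differential editing could therefore bias group contrasts and within-patient change, with unknown sign and a size that cannot be derived from the documents. The shifts of 0.1 to 0.5 SD used above are assumptions that show sensitivity; they are not estimates. The two-minute threshold adds little and is not needed for the conclusion.

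The documents do not show that reviewers will see group or visit, or that any bias has occurred. The study's exploratory status limits the consequence. The point is a cheap, worthwhile improvement to a stated rule, and its main benefit is to the longitudinal objectives.

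**What to change.** Limit the section 2.3 sentence to the clinical interview and rating. Then state in section 2.5 that diarization and transcript review is done:

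- on files recoded by script to a random identifier carrying no participant type, participant code or visit number;
- in shuffled order within batches, which fits staggered recruitment and quality control after every visit;
- without access to MADRS, CGI or PHQ-9 scores;
- where feasible, not by the clinician who conducted that interview.

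Hold the linking key until the feature matrix is locked.

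The cost is a renaming script and a few sentences of text. Separating reviewer from interviewer may need extra staff, since the article does not say who reviews; hence the qualifier. Masking of group will remain partial because content often reveals it. Recruitment and data collection run to December 2027 and analysis is planned for February 2028 (section 2.10), so the change can still be made. It affects processing only. If judged substantial, it follows the amendment route in section 3.3. Recordings already reviewed can be re-reviewed from the preserved originals.
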